**Table 1 Tab1:**
[figure not shown]
Overview of clinical and radiologic follow-up. *CT* computed tomography, *MRI* magnetic resonance imaging, *SF-12* 12-item Short Form Health Survey, *VAS pain* visual analog scale for pain

MRI images will be assessed by a senior radiologist for degenerative changes of the tibiotalar joint and the syndesmosis structure (unaffected, hyperintense signal alteration on T2, partial tear, complete tear), widening, and calcification. By using questionnaires preoperatively and postoperatively after 6 weeks and 3, 6, and 12 months during the appointments, patients can provide information on pain, mobility of foot and ankle, and quality of life (SF-12) [19] during the course of treatment. General patient data, including age, profession, body mass index (BMI), risk factors, medication, concomitant diseases, previous surgeries, and details of the accident, will be documented preoperatively.

At 25 weeks postoperatively, patients also receive a gait analysis and MRI is performed to assess motion anomalies and the healing process of the syndesmosis.

The planned study will run over 2 years. Patients will be admitted over a period of 1 year. Each patient will be treated and followed-up over a 12-month period.

All data will be stored and monitored using pseudonyms. The data of all patients will be analyzed statistically and compared at the end of the 2 years (Table 1).

Furthermore, all data of the participating patients will be carefully assessed, and all adverse events and complications of the treatment will be reported at the end of this trial. The harms will be categorized according to their degree of severity in either serious or non-serious.

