### Sample size calculation and statistical analyses

Formal sample size determination is not possible as potential effects are not yet known. Data from previous studies were utilized to determine the necessary sample size [23–25]. We plan a sample size of 25 patients, who will be treated with the cortical screw fixation and 25 patients, who will be treated with the dynamic TightRope® system within 2 years. The patients will be randomized to the two different treatment options. The randomization will be independent of the surgeon and the doctor who will do the examinations and the questionnaires.

The Shapiro-Wilk test will be used to check if our population is normally distributed. Standard unpaired Student’s *t* test to detect significant changes between the two groups will be conducted, if they are normally distributed. In contrast, possible differences for continuous data and scores between groups will be evaluated with the Wilcoxon *U* test, if no normal distribution exists.

The empirical distribution of continuous data and scores will be reported and calculated with means, standard deviation (SD), median, minimum, and maximum values and with absolute and relative frequencies for categoric data as well as unpaired *t*-test *p* values to depict a significant difference between the different groups. All descriptive analyses will be calculated for demographic data and for the dependent variables derived from the functional assessment, gait analyses results, and questionnaires of both groups.

An independent senior statistician of the Institute of Medical Biometry and Informatics of our university will perform the analysis. The intention-to-treat population will be used.

The analysis and illustrations will be carried out by use of SPSS version 25.0 for 135 Windows (IBM Corp., Armonk, New York, USA) and GraphPad Prism version 6.00 for Windows (GraphPad Software, San Diego, California, USA). For the representation of statistical relationships, the Pearson correlation coefficient will be used. The final details of the statistical analysis will be established in a statistical analysis plan, which will be completed before the closing of the database (before the end of data collection). A *p* value of ≤ .05 will be used to indicate statistical significance. Only a complete follow-up examination will be considered in the statistical analyses.

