### Secondary outcome measures

Secondary endpoints and measurements will be recorded 6 weeks and 3, 6 and 12 months postoperatively. The measurements include different questionnaires mentioned above with subjective evaluation of the quality of life (assessed by the 12-item Short Form health survey [SF-12] questionnaire) [19] and pain (visual analog scale [VAS]). In addition, a self-designed questionnaire as well as the “Score of Olerud und Molander (OMAS)” [20] and “Foot and ankle outcome score (FAOS)” [27] will be used to evaluate the range of motion, deficits in daily life, symptoms after ankle fractures and after surgical treatment, and socioeconomic factors (period of time, returning back to work, and time of recovery).

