The large number of 50 patients is also remarkable. Moreover, only experienced orthopedic trauma surgeons will perform all surgical procedures which improve good external validity. The objective biomechanical outcome measurements with the aid of gait analysis are a unique characteristic which can show kinematics and functions of the ankle joint.

Limitations of the study include the diversity of ankle injury and fracture types that can bias the outcome. To minimize bias, all included patients will follow the same postoperative weight-bearing pattern.

We only perform CT/3D imaging on the fracture site. A bilateral CT investigation to detect possible anatomical variations will not be performed. A 1-year follow-up involves the danger of not being able to detect long-term complications as degenerative changes or osteolysis that could be a result of either a malreduced syndesmosis or an initially unreported osteochondral lesion. Therefore, a longer follow-up period would be interesting to observe such possible changes in the ankle mortise (widening, osteolysis, or osteoarthrosis).

Our hypothesis is that TightRope® will provide the same biomechanical, clinical, and radiological outcome with a similar or better postoperative function of the ankle in the gait analysis. Furthermore, we assume that the recovery time and the time required to return to work is shorter in the TightRope® cohort than in the static screw control group.

The results of the study should, in biomechanical terms, therefore help to demonstrate the comparability of different treatment methods by using the gait analysis as an objective and modern measurement method.

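### Return to work and recovery time: the t test/Wilcoxon rule on complete follow-up discards known times of patients lost early and gives no way to handle those not back by 52 weeks

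*Protocol article*

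**What the plan says.** All references are to the protocol article.

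- **Outcomes.** Secondary outcome measures lists, among the questionnaire items, "socioeconomic factors (period of time, returning back to work, and time of recovery". The same section sets the schedule: "Secondary endpoints and measurements will be recorded 6 weeks and 3, 6 and 12 months postoperatively".
- **Expectation.** The Discussion states as an assumption: "the recovery time and the time required to return to work is shorter in the TightRope® cohort than in the static screw control group". This is not part of the H0/H1 pair under Objectives and hypotheses.
- **Follow-up.** The Follow-up section gives one common end point: "Each patient will be treated and followed-up over a 12-month period".
- **Test.** Sample size calculation and statistical analyses prescribes an unpaired t test for normally distributed data. Otherwise, "possible differences for continuous data and scores between groups will be evaluated with the" Wilcoxon U test. Means, SDs and t-test p values are to be reported for the questionnaire variables. No time-to-event method is named.
- **Who counts.** The same section adopts the intention-to-treat population and then adds: "Only a complete follow-up examination will be considered in the statistical analyses". It leaves final details to a statistical analysis plan.

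**The concern.** These two outcomes are durations observed through a 12-month window. Some patients may not have the event inside that window, and some may leave before it closes. A t test, and a Wilcoxon test without a coding rule, both need a finished time for every patient.

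The patients without a finished time are those with the worst outcomes or those who left early. A comparison among returners conditions on something that happens after randomisation and may itself differ by arm. Only the screw arm has a planned second operation, and the Discussion links that operation to missed work days and longer recovery. The Discussion also says that up to 30% of ankle-fracture patients report residual symptoms. It gives no time point, but it makes full recovery of everyone by 52 weeks an unsafe assumption.

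At stake is whether the trial can show a difference that its Discussion expects.

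**Working it through.** **1. No figure in the plan to reproduce.** The article plans 25 per arm and gives no effect, SD, power or return rate for these outcomes. All sizes below rest on assumed inputs.

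**2. What the stated rule does to three kinds of patient.**

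- *Back at work at week 10, lost at month 9.* The time is known, but follow-up is incomplete, so the rule discards it. This sits badly with the intention-to-treat statement in the same section.
- *Seen at every visit, still off work at 52 weeks.* Follow-up is complete, so the rule does not exclude this patient. There is no numeric time, so the t test, mean and SD cannot use the patient. Wilcoxon can, if the patient is ranked last, but no such coding is stated.
- *Lost at month 9, still off work.* Excluded, although nine months off work are known.

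**3. Size of the masking, by hand.** Assume log-normal return times with median 10 weeks and log SD 0.5 in both arms, and 5% (TightRope) versus 25% (screw) not back at 52 weeks.

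- Mean among returners = median × exp(SD²/2) = 10 × exp(0.125) = 11.3 weeks in each arm, so the returners-only difference is 0.
- Restricted mean to week 52 ≈ (1 − p) × 11.3 + p × 52.
- Difference = (0.25 − 0.05) × (52 − 11.3) = 0.20 × 40.7 = 8.1 weeks.
- Simulation (4,000 trials, 20 per arm) gives 0.02 and 8.12 weeks.

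**4. With a true shift as well (medians 10 and 13 weeks).** Means among returners are 11.3 and 13 × exp(0.125) = 14.7 weeks, a difference of 3.4.

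- 5% versus 15% not back: (0.85 × 14.7 + 0.15 × 52) − (0.95 × 11.3 + 0.05 × 52) = 20.3 − 13.3 = 7.0 weeks. Simulated: 6.93, against 3.36 among returners.
- 5% versus 25% not back: (0.75 × 14.7 + 0.25 × 52) − 13.3 = 24.0 − 13.3 = 10.7 weeks. Simulated: 10.64, against 3.32 among returners.

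**5. Power, same assumptions, 20 per arm, two-sided 0.05.** The last-rank column and the equal-5% row come from a further run of 2,000 trials, which also gave the second log-rank values.

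| Not back, TightRope/screw | Wilcoxon, returners only | Wilcoxon, all, non-returners last | Log-rank |
|---|---|---|---|
| none | 0.344 | – | 0.344 |
| 5%/15% | 0.311 | 0.445 | 0.441; 0.438 |
| 5%/25% | 0.298 | 0.629 | 0.658; 0.668 |
| 5%/5%, true shift | 0.33 | – | 0.24 |
| 5%/5%, no difference (type I error) | 0.049 | – | 0.058 |

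**6. Dependence on the non-return share.** A second model has 25 per arm, proportional hazards, a hazard ratio of 2 for return and 3,000 trials.

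| Screw arm not back | t / Wilcoxon, returners only | Wilcoxon, all, last rank | Log-rank |
|---|---|---|---|
| 2% | 0.59 / 0.49 | 0.52 | 0.65 |
| 10% | 0.42 / 0.37 | 0.53 | 0.66 |
| 20% | 0.25 / 0.22 | 0.50 | 0.60 |
| 30% | 0.18 / 0.16 | 0.51 | 0.60 |

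The loss comes from leaving patients out, not from the Wilcoxon test as such.

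**The case against.** A reader might infer that the rule drops everyone not back at work by 12 months. The document does not support that. Such a patient, if seen, has a complete examination; no sentence excludes that patient; and with a common 52-week end point Wilcoxon can keep all of them at the last rank, with power close to log-rank. This objection stands and limits the point.

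Four further objections have weight:

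- The non-return shares are assumptions. The article suggests neither many nor few, and the contrast of 0 against 8 weeks needs a 20-point gap between arms.
- A censored-time test is not uniformly better. With equal 5% non-return and a true shift, log-rank has less power than the returners-only test. The second model shows the same at 4% in each arm (0.34 against 0.49 to 0.50).
- The expectation is an assumption in the Discussion about secondary outcomes of a pilot, listed as socioeconomic factors. It is not a tested hypothesis. The article does not define these items as durations, so placing them under the continuous-data rule is itself a reading.
- Final details are left to an analysis plan that is not shown, and coding unfinished times is a usual item there.

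The last objection does not dispose of the point. The article itself fixes the tests and the complete-follow-up restriction, and moving to censored times or exempting an outcome changes what is written. Loss before 12 months does affect every outcome, but here it also throws away times that are already known.

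**Conclusion.** The point holds in a limited form, as an inexpensive improvement for two secondary outcomes.

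From the text: the stated rule discards known return times of patients lost before 12 months, and its t test and means cannot use patients without the event by 52 weeks.

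Conditional: if those patients are left out and non-return differs between arms, the difference is understated. Under the assumed inputs, returners alone show 0 weeks where the restricted mean differs by about 8, or about 3.4 where it differs by about 7 to 11. Where non-return is rare and equal, nothing is masked.

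The main argument is validity, since the comparison should not condition on having returned. The power gain depends on a non-return share that the article does not give.

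**What to change.** In the statistical analysis plan:

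- Exempt return to work and recovery time from the complete-follow-up restriction.
- Analyse each as time from surgery to event, censored at last contact or 52 weeks; for return to work, among patients working at the time of injury.
- Show Kaplan-Meier curves and report the difference in restricted mean time to 52 weeks with its 95% interval.
- Name one test in advance: log-rank, or Wilcoxon with non-returners seen at 12 months ranked last. Log-rank also uses patients lost before returning; the ranked version needs a separate rule for them.

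The cost is a few sentences before database closure and routine software. The downside is the log-rank loss when non-return is rare and equal in both arms (about 0.24 against 0.33) and a type I error slightly above nominal at this size (about 6%).

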### Trial status

The RCT trial is ongoing (study protocol version 1.0 02.08.2017, S-454/2017), patient recruitment, and surgical treatment began in December 2017. Recruitment is expected to be completed in December 2019. The follow-up is conducted over a 12-month period for each patient included. Data analysis will only be performed after complete 1-year follow-up. Thereafter, the final results will be published.

### Study beginning

The acquisition of study participants started after receiving the approval of the trial protocol by the local ethics committee.

## Data Availability

The datasets used and analyzed during the current study are available from the corresponding author on reasonable request.

## Abbreviations

AO: “Arbeitsgemeinschaft für Osteosynthesefragen”
BMI: Body mass index
CT: Computed tomography
MRI: Magnetic resonance imaging
OMAS: Score of Olerud und Molander
ORIF: Open reduction and internal fixation
SF-12: 12-item Short Form Health Survey
VAS pain: Visual analog scale for pain
